##### Cardiopulmonary exercise test (CPET)

The CPET is administered as part of the screening/baseline assessment and is repeated at the 18-month follow-up. It provides a measure of maximal oxygen consumption, VO_2peak_, an index of cardiorespiratory function and aerobic fitness. Participants are asked to refrain from food and drink for 4 h, except clear liquids, and abstain from caffeine for 12 h before the test. A resting 12-lead ECG is obtained initially in the supine and standing positions to determine possible contraindications to exercise testing. Participants are fit with a mouthpiece and nose clips for the measurement of cardiopulmonary data. All participants complete a maximal graded exercise test with gas analysis to measure peak aerobic capacity. The CPET is completed on an upright stationary cycle ergometer utilizing an individualized ramp protocol with the ramp set to elicit a test duration of approximately 8–12 min. Cardiopulmonary data is assessed via calibrated open-circuit spirometry. During the CPET, participants are instructed to maintain a consistent cadence throughout the entire test as the workload increases. The cycle ergometer ramp test increases watts by 12.5, in a ramp fashion, every minute until the participant reaches volitional exhaustion or satisfies the stopping criteria from the American Heart Association/American College of Sports Medicine. A 12-lead electrocardiogram is continuously monitored, and manual blood pressures are taken during the last 30 s of each stage of the test. Two criteria establish maximal effort: (1) a respiratory exchange ratio (CO_2_/O_2_) greater than 1.10, and (2) a Borg rating of perceived exertion greater than 7 on a 10-point scale. The CPET is a primary CYCLE-AD study outcome (Table 2).

##### Biomechanical gait analysis

The Computer Assisted Rehabilitation Environment (CAREN) system (Motekforce Link, Amsterdam, Netherlands) is used to quantify gait and postural stability (Baron et al., 2018; Penko et al., 2018; Rosenfeldt et al., 2019a; Rosenfeldt et al., 2019b). The system consists of a fully integrated Vicon 3D motion capture system, a treadmill, force plate platform, a 180° curved projection screen, and a safety harness. The modified Plug-In Gait marker model is used with 35 retro-reflective markers placed on anatomic landmarks. The 10-camera Vicon system, in combination with D-Flow software, captures the 3D position of each marker at 100 Hz. The primary gait measure is self-paced gait velocity (m/s) over a 1-min walk test with and without performing a secondary cognitive task, enabling an analysis of dual-task performance. Secondary measures include step length, step width, cadence, and arm swing (Baron et al., 2018). The limits of stability (LOS) test is a secondary outcome used to evaluate postural control (Pickerill and Harter, 2011) under single- and dual-task conditions. The force plate in the CAREN system is used to quantify the maximum distance an individual can displace their center of mass within their base of support in eight different directions. The primary postural control outcome is the sway area, the center of pressure area (cm^2^) throughout an 80-s trial.

##### Physical function testing

Participants complete a 6-minute walk test (6MWT). The primary measure is the total distance walked in 6 min. Heart rate and ratings of perceived exertion are also measured. Functional mobility is measured using the Timed Up and Go (Miller Koop et al., 2018; Miller Koop et al., 2019), 10 meter walk, and 5× sit to stand tests, which are completed using validated iPad applications (Ozinga and Alberts, 2014; Ozinga et al., 2015; Ozinga et al., 2017a; Ozinga et al., 2017b). Briefly, the iPad is attached at the sacral level of the participants during the performance of these clinical tests. Data gathered from the iPad IMUs (accelerometer and gyroscope) are used to calculate biomechanical measures of gait, postural stability, and specific phases (including turning velocity) of mobility assessments.

##### Quality of life questionnaires

Quality of life is assessed with the World Health Organization Quality of Life for Older Adults (WHOQOL-OLD) (Power et al., 2005). The Self-Efficacy for Exercise Scale is used to assess the ability to continue exercising in the face of barriers (Resnick and Jenkins, 2000).

#### Neurocognitive assessment

The standardized neuropsychological test battery consists of measures of premorbid intelligence, episodic memory, information processing speed, executive functions, and sustained attention. The test battery includes the Wide Range Achievement Test 4 (WRAT4) (Wilkinson and Robertson, 2006), Rey Auditory Verbal Learning Test (RAVLT) (Rey, 1958), Brief Visuospatial Memory Test-Revised (BVMT-R) (Benedict, 1997), Delis Kaplan Executive Function System (sorting test) (Delis et al., 2001), Stroop Test (Golden and Freshwater, 2002), Controlled Oral Word Association Test (COWAT) (Benton et al., 1983), Boston Naming Test (BNT) (Kaplan et al., 2001), Trail Making Test A and B (Reitan, 1958), Judgement of Line Orientation (JOLO) (Lindgren and Benton, 1980), Wechsler Adult Intelligence Scale IV (WAIS-IV) Digit Span (Forward, Backward, and Sequencing) (Wechsler, 2008), Rey-Osterrieth Complex Figure Copying Test (Rey, 1941; Osterrieth, 1944), Processing Speed Test (Rao et al., 2017), and Visual Memory Test (Rao et al., 2023). Where available, counterbalanced, alternate equivalent forms are used to minimize practice effects. The 5-trial total recall on the RAVLT is a primary outcome for the CYCLE-AD trial (Table 2).

#### Magnetic resonance imaging

MRI is conducted on a Siemens Prisma 3T MRI scanner with a 32-receive channel head coil. Participant motion is minimized using a bite bar. A molded dental impression (Kerr Dental, Inc., Brea, CA, USA) is taken of the subject’s teeth. This mold is affixed to a plastic frame placed over the head coil. The subject is asked to place their teeth into the mold during active scanning. Including patient preparation and scanner tuning, this protocol is accomplished in 90 min. Preliminary scans include a localizer and two -GRE B0 field maps. Detailed scan parameters are provided in Table 3. The following section provides information on the collection and analysis of each scan.

**TABLE 3 T3:** Detailed scan parameters for MRI protocol.

Scan						
**Sequence parameter**	**3D T1**	**High Resolution Hippocampus**	**3D FLAIR**	**CBF**	**Resting State fMRI**	**Diffusion MRI* **
Sequence	MPRAGE	Turbo Spin Echo	SPACE	3D Pulsed ASL	SMS GRE-EPI	SMS-SE-EPI
Scan plane	Sagittal	Coronal	Axial	Axial	Axial	Axial
Time of acquisition (min:sec)	5:21	4:18	5:17	5:40	6:01	7:55
FOV (mm^2^)	256′256	175′175	256′256	240′240	260′260	220′220
Matrix	256′256	448′448	256′256	64′64	104′104	110′110
Voxel size (mm)	1′1′1	0.4′0.4′2	1′1′1.2	3.75′3.75′4.5	2.5′2.5′2.5	2′2′2
TI	900 ms	N/A	1,800 ms	800/2,000 ms	N/A	N/A
TE	2.98 ms	52 ms	393 ms	20.25 ms	29 ms	75 ms
TR	2,300 ms	8,000 ms	5,000 ms	4,000 ms	1,360 ms	2,700 ms
Flip angle	9°	150°	variable	180°	65°	90°
Receiver bandwidth (total)	61.44 kHz	17.675 kHz	200 kHz	156 kHz	227 kHz	250 kHz
Partial Fourier	N/A	N/A	N/A	N/A	8-Jul	8-Jun
GRAPPA	2	2	2	none	None	none
(ACC/ACS)						
SMS	N/A	N/A	N/A	N/A	3	3

*Additional information for dMRI: 8/30/17/60 diffusion weightings of 0/7/1,000/2,800 s/mm^2^ b = 2,800 s/mm^2^ are acquired. Following the diffusion acquisition, an 18 s phase-reversed b = 0 volume is acquired to be used for post-processing distortion correction.

##### Anatomical imaging (3D T1-weighted scan)

Total hippocampal volume (right plus left) is a primary outcome for the CYCLE-AD trial (Table 2) and is calculated using the MPRAGE in Freesurfer (7.4.1) (Iglesias et al., 2015). Individual differences in head size are corrected for by allometric scaling (Liu et al., 2014) or by using log(ICV) as an adjustment regressor (Williams et al., 2021). In addition, the ADNI high-resolution hippocampal scan is used to calculate hippocampal subfield volumes in ASHS (ashs-1.0.01) (Xie et al., 2016). Measures of interest include the sum of CA1, CA2, and CA3, the dentate gyrus, and the subiculum.

##### Resting-state functional connectivity (rs-fMRI)

Functional connectivity between the hippocampus and the posterior cingulate is measured using the resting-state connectivity scan. During scanning, respiratory and cardiac signals are sampled at 400 Hz using a plethysmograph and respiratory bellows. These signals are regressed using RETROICOR (Glover et al., 2000) as provided by AFNI. If physiologic signals are not recorded, they are estimated using PESTICA (pestica_afni_v5.521) (Beall and Lowe, 2007). Volumetric and slice-based motion are estimated and corrected using SLOMOCO (slomoco_afni_v5.52) (Beall and Lowe, 2014; Shin et al., 2022). Motion and physiologic noise estimates are regressed simultaneously. An estimate of voxel-level residual displacement is used to characterize motion artifact in each scan for use in summary statistics and quality control. The measure of interest is the normalized strength of functional connectivity measured between the posterior cingulate seed and the hippocampus (Koenig et al., 2021a).

##### Diffusion tensor imaging (DTI) anatomical connectivity

Structural connectivity of the hippocampus and posterior cingulate is measured using a DTI scan. Preprocessing includes distortion correction with topup and motion (Andersson and Sotiropoulos, 2016), and eddy current (Jenkinson et al., 2012) correction (FSL 6.0.7.12). The left and right ventral cingulum bundles are identified using Freesurfer 7.4.1 and tracked using TRACULA (Maffei et al., 2021). Measures of interest include average axial and radial diffusivity along the bilateral ventral cingulum bundle.

##### Three-dimensional arterial spin labeling (3DASL)

Hippocampal and cortical gray matter blood flow is calculated using the 3DASL scan. Data are preprocessed using AFNI (AFNI_24.0.02) (Cox, 1996) and oxford_asl (FSL 6.0.7.12) (Chappell et al., 2009). The hippocampal region of interest (ROI) is taken from the Freesurfer analysis. The posterior cingulate ROI is extracted from the Yeo 7 Network parcellation of the default mode network (Yeo et al., 2011). Voxels are restricted to those composed of ≥ 70% gray matter. Measures of interest are the average perfusion in ml blood / 100 g tissue / min. in each ROI.

##### White matter hyperintensities (WMHs)

WMH volumes are calculated from T2 Fluid Attenuated Inversion Recovery (FLAIR) scans. WMHs are calculated using the LST-AI software^3^ (Wiltgen et al., 2024). The measure of interest is lesion volume in mm^3^.

#### Blood biomarker analyses

All blood samples are collected in the morning after fasting for 12 h. Plasma analyses (Weber et al., 2020; Koenig et al., 2021b; Weber et al., 2022) include measurements of anti-inflammatory (IL-4, IL-6, IL-10, IL-13, sTREM2), pro-inflammatory (IFN-γ, TNF-α, IL-1β, IL-6, MCP-1), neuronal (BDNF, NFL, NSE, Neurogranin), and AD-related (Abeta40, Abeta42, p-tau181, t-tau) biomarkers. Changes in biomarkers over the 18-month intervention interval serve as tertiary outcome measures.

### Statistical analysis

#### Sample size and power

The CYCLE-AD RCT will compare changes from baseline to 18 months on the primary and secondary outcomes (see Table 2) in the UCC and IC randomized groups (75 per group). The sample size was estimated for each of the three primary outcomes: (1) trial 1–5 total recall on the RAVLT (RAVLT_*T1–5*_), (2) total hippocampal volume (THV), and (3) VO_2peak_. To determine the sample size necessary to detect a clinically meaningful difference between the groups for each primary outcome, we first estimated the variability (standard deviation) of the changes over 18 months in each variable from previous studies. Data for RAVLT_*T1–5*_ and THV are derived from our 18-month longitudinal study comparing high and low PA APOE ε4 carriers (Woodard et al., 2012; Smith et al., 2014); data for VO_2peak_ are derived from a published study (King et al., 1991). For each outcome, we calculated the pooled SD (combining intervention groups), and since the pooled SDs are only an estimate of the variability of changes that were observed from each study, we increased the pooled estimate to be equal to the upper 90th percentile of the SD distribution for each primary outcome. The assumed pooled and inflated SDs are: 17.15% for RAVLT_*T1–5*_, 4.35% for THV, and 3.16 ml/kg-min for VO_2peak_. Secondly, the size of the clinically meaningful difference to be detected between the groups for each outcome was determined based on the observed values seen in these previous studies. The differences to detect for changes over 18 months are: 9.5% for RAVLT_*T1–5*_, 2.4% for THV, and 1.75 ml/kg-min for VO_2peak_. These differences are similar to those actually observed in the cited studies and were selected to give similar sample sizes so that each aim would have adequate power with the same sample size. Hence, the detectable differences and SDs given above resulted in an estimated sample size for each primary outcome of 68 per group, assuming a power of 90% and a significance level of 5% (two-sided). Furthermore, we estimated that up to 10% of participants will not complete the 18-month measurements. Therefore, we inflated the sample size of 68 per group by 10%, yielding a study sample size target of 75 per group.

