**Design:**

CYCLE-AD is a randomized, single-blind, single-center, controlled trial of a home-based, high-intensity exercise intervention involving 150 older ε4 carriers (ages 65–80 years) who are healthy, cognitively unimpaired, and physically inactive. Participants are randomized into two groups: indoor cycling (IC) or usual and customary care (UCC) (target of 75 each). IC participants exercise 3×/week on an upright stationary cycle ergometer at a moderate-vigorous intensity for 18 months. Those in the UCC group are expected to maintain enrollment levels of activity.

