**FIGURE 1 F1:**
[figure not shown]
CYCLE-AD flow of study trial events.

**TABLE 1 T1:** Schedule of CYCLE-AD trial events.

Procedures	ICF visit	Screening visit (Within 90 days of ICF)	Baseline visit (Screening visit +30 days minimum)	9 month F/U (Day 0* + 9M ± 15 days)	18 month F/U visit (Day 0* + 18M + 30 days)
Informed consent	X				
APOE genotyping	X		X		
Telephone screening	X				
30-day pre-intervention physical activity		X			
Randomization and enrollment		X			
Cardiopulmonary exercise test (CPET)		X			X
Computer Assisted Rehabilitation Environment System			X		X
3T magnetic resonance scanning			X		X
Plasma biomarker collection/analyses			X		X
Indoor cycle fitting		X			
Peloton-garmin monitoring check-in			X	X	X

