**Neurocognitive test battery**					
Wide Range Achievement Test 4, Reading			X		
Rey Auditory Verbal Learning Test (RAVLT)			X	X	X
Brief Visual Memory Test–Revised (BVMT-R)			X	X	X
Stroop Color and Word Test			X	X	X
Controlled Oral Word Association Test			X	X	X
Trail Making Test (A and B)			X	X	X
Delis Kaplan Executive Function System (DKEFS)–Sorting			X		X
Rey–Osterrieth Complex Figure Copy Test			X		X
Boston Naming Test			X		X
Judgement of Line Orientation			X		X
Processing Speed Test			X	X	X
Visual Memory Test			X	X	X
Wechsler Adult Intelligence Scale (WAIS) IV, Digit Span			X	X	X

*DAY 0 = ≤ 30 days of completion of baseline visit.

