### Baseline and follow up assessments

Enrolled participants complete three in-person outcome assessment visits: (1) Pre-Intervention Baseline (0-month), (2) Mid-Intervention (9 months), and (3) End-of-Intervention (18 months). The baseline and 18-month visits are typically conducted over two days and are scheduled within two weeks of each other. The abbreviated 9-month visit is conducted over a single day. Tests performed during each visit are shown in Table 1 and described below. The total study participation time is approximately 19 months, extending from a 30-day physical activity pre-intervention baseline (see below) to the post-intervention 18-month follow-up assessment. Primary and secondary outcomes for the CYCLE-AD trial are listed in Table 2.

**TABLE 2 T2:** Primary and secondary outcomes for CYCLE-AD trial.

Outcomes	Exercise	Cognition	MRI
Primary	Cardiopulmonary exercise test (VO_2peak_)	RAVLT (total recall trials 1–5)	Anatomical MRI (total hippocampal volume)
Secondary	CAREN biomechanical gait (velocity in m/s)	Episodic memory: RAVLT delayed recall; BVMT-R, Visual Memory Test	Anatomical MRI (hippocampal subfields)
	CAREN postural stability (sway area in cm^2^)	Processing speed: Trail Making Test A, WAIS IV Digit Span, Processing Speed Test	Resting-state functional connectivity (between hippocampus and posterior cingulate)
	Physical function battery (time up and go, 10 meter walk, 6 minute walk test, and 5× sit to stand)	Executive functions: DKEFS (sorting), Stroop Color and Word Test, Trail Making Test B	Diffusion tensor imaging (anatomical connectivity between hippocampus and posterior cingulate)
	Garmin Vivofit 4 Health Monitor (number of steps)	Visuospatial abilities: Judgement of Line Orientation, Rey–Osterrieth Complex Figure Copy Test	Three-dimensional arterial spin labeling (hippocampal and cortical gray matter blood flow)
	Self-report quality of life questionnaires	Language: Boston Naming Test, Controlled Oral Word Association Test	Fluid Attenuated Inversion Recovery (white matter hyperintensities)

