#### Physical activity (PA) monitoring

All enrolled participants are provided a Garmin Vivofit 4^2^ device to measure steps per day throughout the trial. Participants are instructed to wear the device on their ankle (with a provided band) during waking hours for the entire 18-month trial duration. Additionally, PA baseline monitoring is obtained by having participants wear the device for 30 days before the baseline assessment. Participants are asked to synchronize the device with the Garmin Connect application installed on their mobile device or tablet on a weekly basis. Project personnel pull data from the Garmin portal weekly with an automated script to a secure HIPAA-compliant server behind the Cleveland Clinic firewall. The transfer process is completed weekly for each participant and stored on a secure shared drive. PA monitoring for both groups is supervised by an exercise physiologist.

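### Exploratory step-count outcome: the baseline-to-month-18 contrast spans about half a year of season, which adds avoidable noise between arms and blurs any within-arm reading

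*Protocol article*

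**What the plan says.** Table 2 (Baseline and follow up assessments) lists "Garmin Vivofit 4 Health Monitor (number of steps" among the secondary outcomes. Under Physical activity (PA) monitoring, "PA baseline monitoring is obtained by having participants wear the device for 30 days before the baseline assessment", and the device is then worn "during waking hours for the entire 18-month trial duration", with weekly data pulls.

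The contrast is given under Sample size and power: "The CYCLE-AD RCT will compare changes from baseline to 18 months on the primary and secondary outcomes (see Table 2", and the same sentence makes this a comparison of the two randomised groups. Data analysis applies analyses similar to the primary ones to the secondary outcomes and labels them exploratory. It allows ANCOVA with prespecified baseline covariates, naming sex, race, age and education as examples. Season is not named.

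Table 1 sets the last visit as "18 month F/U visit (Day 0* + 18M + 30 days", and its footnote reads "DAY 0 = ≤ 30 days of completion of baseline visit". The article does not define which days make up the month-18 step value.

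The Design paragraph of the Abstract adds the premise for the control arm: "Those in the UCC group are expected to maintain enrollment levels of activity".

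**The concern.** Daily steps plausibly vary with season. A baseline window in January is set against roughly July, and one in July against roughly January. Part of each person's change score can therefore be season and not a change in habit. The wording of the contrast leaves this in, although the device also records the same calendar period one year after baseline.

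Two things are at stake, both modest. The first is precision in the arm comparison of steps. The second is the meaning of the mean change within one arm: a reader who looks at it to see whether UCC participants stayed at their enrolment level would see season mixed in, and randomisation does not remove season from a within-arm change.

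**Working it through.** The article states no step-count figure to reproduce. Its 68 per group is derived for the three primary outcomes and is used here only as the number analysed per arm.

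**1. Season offset (Table 1).** Day 0 is up to 30 days after the baseline visit, and the last visit is at Day 0 + 18 months, plus up to 30 days. The spacing is therefore 18 to 20 months. Modulo 12 that is 6 to 8 months, against 0 for a 12-month contrast. For a yearly sinusoid, the share of the largest possible seasonal contrast is |sin(π × offset/12)|:
- 18 months: 1.00
- 19 months: 0.97
- 20 months: 0.87

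**2. Seasonal part of one person's change.** Let D be the summer-winter swing (assumed 600-1,200 steps/day). A half-year shift changes the score by D × cos(phase at entry). This is ±D for midsummer or midwinter entry and about 0 for mid-spring or mid-autumn entry. With entry spread evenly over the year, the mean is 0 and the SD is D/√2:
- D = 600: SD 424
- D = 1,200: SD 849

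**3. Extra variance in the arm comparison.** Let s be the non-seasonal SD of change (assumed 1,500-2,000). The variance ratio is (s² + D²/2)/s²:

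| D | s | ratio |
|---|---|---|
| 600 | 2,000 | (4,000,000 + 180,000)/4,000,000 = 1.045 |
| 600 | 1,500 | (2,250,000 + 180,000)/2,250,000 = 1.08 |
| 1,200 | 2,000 | (4,000,000 + 720,000)/4,000,000 = 1.18 |
| 1,200 | 1,500 | (2,250,000 + 720,000)/2,250,000 = 1.32 |

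Take a difference that would have 90% power at 68 per arm without season. Power becomes Φ(3.24/√ratio − 1.96), which is about 89% at 1.045 and about 81% at 1.32. At D = 1,000 and s = 2,000 the ratio is 1.125, power is 86.3%, and 77 per arm would restore 90%. Over a wider set of assumptions (D 500-2,000, s 1,500-3,000) the extra variance runs from 1.4% to 89%.

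**4. Bias between arms.** With D = 1,000, s = 2,000, no true effect, 68 per arm and 20,000 simulated trials, the mean arm difference was 3.6 steps (year-round entry) and −5.3 steps (all entry in summer). Type I error was 5.1% and 4.8%. A shared seasonal shift cancels.

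**5. Shift within an arm.** In the same simulation, the mean change within an arm was about 0 with year-round entry and about −900 with all entry in summer, that is 0.9 × D. If 40% enter in summer and 20% in each other season, the shift is 0.9 × (0.4 − 0.2) = 0.18 × D in size, or 108 to 216 steps/day for D of 600 to 1,200.

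**The case against.** The strongest reply is that the stated analysis compares randomised groups. Permuted blocks of 4 and 6 keep the arms concurrent in calendar time, so the comparison is valid as it stands. This is correct, and step 4 bears it out. A reader might infer that the step comparison between arms is biased; the documents do not support that. Bias would need both seasonality that differs by arm and uneven entry. If the IC swing were half that of UCC and everyone entered in summer, the bias would be about 450 steps at D = 1,000; with even entry it is 0. The article shows neither condition, although indoor cycling makes the first conceivable.

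A reader might also infer that contamination of UCC cannot be judged. That goes too far. The article names no within-arm step analysis for this purpose, twice-monthly calls ask about activity, and the device is monitored throughout. UCC is asked not to start high-intensity exercise but may walk, so total steps gauge that restriction only loosely in any season.

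Further, the month-18 step summary is not defined and may be set out in an analysis plan that is not shown. That part is no finding. What stands is that the article fixes the endpoint at 18 months, and any window near that visit is about half a year out of season.

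Finally, the swing and the SD are assumptions, recruitment is partly nationwide so that one common swing is a simplification, and randomisation runs from October 2021 to early 2025, which makes extreme seasonal imbalance unlikely. All of this stands and limits the size of the point.

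**Conclusion.** The point holds as a minor matter of precision and interpretation. The contrast for steps is about half a year out of season for every participant in timing, but not in effect: people who enter in spring or autumn shift little. The arm comparison remains unbiased and carries roughly 5% to 32% avoidable variance under the assumed swing and SD.

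Within-arm changes mix season with real change. It is tempting to say that the UCC mean could be wrong by the full 600-1,200 steps/day, but that needs nearly all entry at one seasonal peak. Moderate imbalance, as in step 5, gives 108 to 216.

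The results rest on a sinusoidal season, one swing common to all participants, and figures for swing and SD that the article does not give. No primary outcome and no part of the sample size depends on this.

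**What to change.** For steps only:

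1. Keep the month-18 contrast, but analyse it by ANCOVA adjusted for baseline steps and for season of the baseline window, entered as calendar month or as one sine/cosine pair.
2. Add a season-matched within-arm summary: the 30 days at month 12 against the 30-day baseline, counted from the baseline window so that the calendar dates coincide.
3. Optionally report mean daily steps over months 7-18 as a supplementary full-year summary. It should not replace the month-18 contrast, because it answers a different question (average activity over a year, not change at the end of the intervention).

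The cost is a few degrees of freedom (2 for the sine/cosine pair, 11 for calendar month) and some wording for one exploratory outcome. No new data are needed, and the change can be fixed before the unblinded analysis that follows the last visits in mid-2026. The main limitation is that the season-matched check sits at month 12, not month 18: no pre-intervention step data match month 18 by season.

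### The 10% loss allowance multiplies where it should divide and the 68 is slightly low, so at the maximum assumed loss 75 per group gives about 89% power, not 90%

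*Protocol article*

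**What the plan says.** The section Sample size and power gives a difference and an SD of the 18-month change for each primary outcome: RAVLT total recall over trials 1 to 5, total hippocampal volume (THV) and VO2peak. It reports that these inputs lead to an "estimated sample size for each primary outcome of 68 per group, assuming a power of 90% and a significance level of 5% (two-sided"). It then expects that as many as one participant in ten will miss the 18-month assessment, and concludes: "we inflated the sample size of 68 per group by 10%, yielding a study sample size target of 75 per group".

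The section Data analysis names a t-test on the change from baseline to 18 months as the primary comparison, with a Wilcoxon rank sum test if the changes are not normally distributed. All randomised participants are to be analysed, with missing 18-month values imputed.

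**The concern.** Two steps of the calculation each lean slightly in the favourable direction.

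- **Loss allowance.** Adding 10% to the number needed is not the same as enrolling enough that the number needed remains after 10% are lost. The first multiplies by 1.10; the second divides by 0.90.
- **Evaluable number.** The 68 is a little below what the printed inputs give, most clearly under the t-test that the plan names.

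At stake is whether the stated 90% power is what 75 per group delivers under the plan's own loss assumption. That figure will be repeated when the trial is reported, so it should be reproducible from the stated inputs.

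**Working it through.** **Inputs, all from Sample size and power**

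- Error rates: "assuming a power of 90% and a significance level of 5% (two-sided"), with equal allocation.
- Differences: "The differences to detect for changes over 18 months are: 9.5% for" RAVLT; "2.4% for THV, and 1.75 ml/kg-min for" VO2peak.
- SDs of change: "The assumed pooled and inflated SDs are: 17.15% for" RAVLT; "4.35% for THV, and 3.16 ml/kg-min for" VO2peak.
- Loss: up to 10%.

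**Step 1. Standardised differences (difference / SD)**

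- RAVLT: 9.5/17.15 = 0.5539
- THV: 2.4/4.35 = 0.5517
- VO2peak: 1.75/3.16 = 0.5538

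**Step 2. Reproduce the 68**

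Normal approximation: n per group = 2 × (1.960 + 1.2816)² / d² = 21.015 / d². The t-test figures are from the exact noncentral-t calculation for two equal groups.

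| Outcome | Normal approximation | Planned t-test |
|---|---|---|
| RAVLT | 68.49 | 69.46 |
| THV | 69.04 | 70.01 |
| VO2peak | 68.52 | 69.50 |

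The stated 68 is reproduced to within about one participant by the normal approximation. Every value in the table is nevertheless above 68. Rounded up, the normal approximation gives 69, 70 and 69, and the t-test gives 70, 71 and 70. The 71 for THV arises only because 70.01 rounds up; at 70 per group its power is 90.0%. A one-sided test would give 56 to 57, so the plan's figure is clearly two-sided.

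Power at exactly 68 per group is 89.6% to 89.8% by the normal approximation and 89.1% to 89.4% by the t-test.

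**Step 3. Loss allowance**

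- As written: 68 × 1.10 = 74.8, so 75.
- As needed: 68/0.90 = 75.6, so 76.
- Check: 75 × 0.90 = 67.5 completers per group, fewer than 68.

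**Step 4. Power with 75 per group, by t-test**

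| Outcome | 10% lost (67.5 per group) | No loss (75 per group) | Largest loss that keeps 90% |
|---|---|---|---|
| RAVLT | 89.2% | 92.1% | 1 − 69.46/75 = 7.4% |
| THV | 88.9% | 91.9% | 1 − 70.01/75 = 6.7% |
| VO2peak | 89.1% | 92.1% | 1 − 69.50/75 = 7.3% |

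By the normal approximation, power at 67.5 per group is 89.4% to 89.6%, still just under 90%.

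**Step 5. What full consistency would need**

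- Loss step alone: 76 per group (152 in total).
- t-test and loss step together: 70/0.9 = 77.8, so 78, or 71/0.9 = 78.9, so 79 (156 to 158 in total).
- Standardised difference detectable with 90% power at 67.5 per group: 0.562, against the assumed 0.552 to 0.554.

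**The case against.** A reader might infer that 68 is a plain error and that the trial is underpowered. The document does not support either.

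- **Method.** No sample-size formula is named, and the normal approximation is in common use. It comes within about one participant of 68.
- **Rounding.** If the printed differences and SDs are themselves rounded, the most favourable values that would still print as shown (9.549/17.1451, 2.449/4.3451, 1.7549/3.1551) give 67.7, 66.2 and 67.9 by the normal approximation, so 68 or fewer for all three. This is an assumption, since the differences may be exact choices. It does not bring the t-test to 68 throughout: the same favourable rounding leaves RAVLT at 68.7 and VO2peak at 68.9.
- **Upper limit.** The 10% is a ceiling. With loss below about 7%, 90% is met.
- **Conservative SDs.** The plan raised each SD to the 90th percentile of its estimated distribution. The uninflated SDs are not given, but a standardised difference only 2% larger than assumed, about what an SD 2% smaller would produce, gives 90.1% to 90.3% at 67.5 per group.

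These points stand and fix the size of the matter: 68 is an approximation on the low side, and the shortfall is smaller than the uncertainty in the SDs. They do not rescue the loss step. No choice of approximation makes 67.5 equal to 68, and an allowance set for losses of up to 10% should hold at 10%.

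Two further defences carry little. Imputing missing 18-month values keeps everyone in the analysis but does not by itself restore the lost information, and the plan sizes on completers. Covariate adjustment might add power, but the document makes it optional, names sex, race, age and education without the baseline outcome value, and gives no correlations from which a gain could be computed.

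**Conclusion.** The point holds as a small arithmetic correction. At the plan's own maximum loss, 75 per group leaves 67.5 completers and power of 88.9% to 89.2% for each primary outcome, about one percentage point below the stated 90%. The loss step alone accounts for one participant per group; the rest comes from 68 being slightly low for the planned test.

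This rests on the printed inputs taken at face value, a two-sided 5% t-test for each outcome, and loss at the full 10% in both groups. It does not show that the design is inadequate: power is about 92% with no loss and stays at 90% up to roughly 7%. How three primary outcomes share the 5% level is a separate question and adds no weight here.

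**What to change.** Keep 150 participants. Replace the closing sentences of Sample size and power with a statement along these lines: about 68 to 70 completers per group are needed for 90% power, depending on the approximation; with 75 randomised per group and 10% loss, power is about 89% for each primary outcome at two-sided 5%; and the standardised difference detectable with 90% power at that loss is 0.562. If a loss allowance is still shown as a calculation, divide by 0.9.

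The cost is a change of wording and a power figure about one point less favourable. No extra participants and no change to conduct are needed. The Introduction places the last randomisation in early 2025, so restating the power is also the practical choice over raising the target.
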